### Data collection and management

All study data are collected and managed using an electronic case report form hosted on a secure, web-based platform (https://amrius.amc.crf.kr, Procuratio, Seoul, Korea). Investigators and trained research coordinators enter relevant clinical, imaging, and laboratory data into the electronic case report form at each surveillance visit. Upon enrollment, each participant was assigned a unique study identification number, which is used throughout the study to maintain data anonymity. A designated data manager performs regular quality checks for completeness and accuracy. All data modifications are recorded and logged for audit trail purposes. Personal identifiers are stored separately from study data and protected using coding procedures. Only authorized personnel (investigators, coordinators, data managers) have access to the full dataset.

### Statistical analysis

Detection rates and the rate of curative treatment will be compared using the Fisher exact test. BCLC stage distribution will be compared using the chi-square test. False referral rates will be compared using Fisher exact test or Poisson regression analysis. Time to tumor detection will be analyzed using Kaplan–Meier methods and compared using the log-rank test. Associations between liver function as assessed by Child–Pugh (ie, Child–Pugh A or B), and surveillance image quality, as well as between image quality and detection or false referral rates, will be examined using chi-square or Fisher exact tests as appropriate. If appropriate, multivariable logistic regression analyses will be used to determine the independent associations between variables. All tests will be 2-sided, with *p*-values <0.05 considered statistically significant. Statistical analyses will be conducted using SAS version 9.2 (SAS Institute Inc., Cary, NC, USA).

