### Sample size

The sample size was calculated based on a 2-sided test for comparing 2 independent proportions, with the primary endpoint being the detection rate of early-stage HCC. Based on prior prospective studies in real-world surveillance settings,^12^,^13^,^14^ we assumed a cumulative prevalence of very early or early-stage HCC of 8% during the study period. The sensitivity of HBP-AMRI was estimated at 90%, and that of US at 35%, reflecting the range observed in surveillance cohorts of patients with cirrhosis.^12^,^13^,^14^ Accordingly, we assumed detection rates of 7.2% for HBP-AMRI and 2.8% for US. To detect a statistically significant difference in detection rates between the 2 modalities, with 80% power and a 2-sided alpha of 0.05, and accounting for an anticipated 5% dropout rate, the total required sample size is 806 participants (403 per arm).

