### Enrollment and allocation

Participants were randomly assigned in a 1:1 ratio to either the HBP-AMRI arm or the US arm using a permuted block randomization method with a random block size of 4. Allocation concealment was ensured through the use of a sequestered code, accessed only after informed consent was obtained. The study is open-label, as both participants and investigators were aware of the surveillance assignment due to the visible procedural differences between US and HBP-AMRI.

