### Outcomes

The primary endpoint of this trial is the detection rate of early-stage HCC, defined as Barcelona Clinic Liver Cancer (BCLC) stage 0 or A.^30^ Detection rate is defined as the number of patients whose BCLC 0 or A HCC is detected using a given surveillance modality, divided by the total number of patients under surveillance with that modality, expressed as a percentage. Secondary endpoints include the false referral rate of BCLC 0 or A HCC, detection and false referral rates of BCLC stage 0 HCC, detection and false referral rates of all-stage HCC, distribution of BCLC stages at initial HCC diagnosis, and the rate at which curative treatment (surgical resection and local ablative therapies including radiofrequency ablation, microwave ablation, and cryoablation) is received. False referral rate is defined on a per-exam basis, calculated as the number of surveillance tests interpreted as positive but subsequently confirmed as non-malignant on confirmatory examination, divided by the total number of surveillance tests performed in that modality arm, expressed as a percentage.

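### The primary comparison is by Fisher's exact test, but 806 patients give 80% power only for an uncorrected two-proportion test; with Fisher the power is about 77%

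*Protocol article*

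**What the plan says.** The Outcomes section fixes the endpoint: "The primary endpoint of this trial is the detection rate of early-stage HCC, defined as Barcelona Clinic Liver Cancer (BCLC) stage 0 or A". It is a per-patient proportion in each arm.

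The Sample size section says "The sample size was calculated based on a 2-sided test for comparing 2 independent proportions" and does not name the test. Its inputs are "we assumed detection rates of 7.2% for HBP-AMRI and 2.8% for US", "with 80% power and a 2-sided alpha of 0.05" and "accounting for an anticipated 5% dropout rate". Its result is "the total required sample size is 806 participants (403 per arm". Allocation is 1:1 (Enrollment and allocation).

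The Statistical analysis section then names a single test for this endpoint, with no alternative: "Detection rates and the rate of curative treatment will be compared using the Fisher exact test". The significance threshold there is a two-sided p below 0.05. Nothing in the article says that the sample size was computed for Fisher's test.

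**The concern.** Fisher's test conditions on the total number of events. When events are few, its attainable significance levels are coarse and its true type I error falls well below the nominal 5%. It therefore needs more patients than an uncorrected z or chi-square test for the same power. If 806 came from the ordinary large-sample formula, the stated 80% describes a test that will not be run.

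What is at stake is the chance of missing a real difference. Part of the 5% error rate the trial may spend goes unused, and borderline results that the sizing test would call significant are lost.

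**Working it through.** **Inputs** (all from the Sample size section): p1 = 8% × 90% = 7.2%; p2 = 8% × 35% = 2.8%; difference 0.044; two-sided alpha 0.05 (z = 1.960); power 80% (z = 0.8416); dropout 5%.

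**Step 1. Reproduce 806.** Unpooled normal formula:

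n = (1.960 + 0.8416)² × [p1(1−p1) + p2(1−p2)] / (p1−p2)²

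= 7.849 × (0.066816 + 0.027216) / 0.001936 = 381.2, rounded up to 382 per arm.

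382 / 0.95 = 402.1, rounded up to 403 per arm, or 806 in total. This matches the plan exactly.

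Other formulas with the same inputs:

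| Method | Evaluable per arm | Randomised per arm | Total |
|---|---|---|---|
| Unpooled normal | 382 | 403 | 806 |
| Pooled normal | 384 | 405 | 810 |
| Arcsine | 367 | 387 | 774 |
| Continuity-corrected (approximates Fisher) | 429 | 452 | 904 |
| Exact Fisher (step 3) | 412 | 434 | 868 |

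Only the uncorrected normal formulas land on or next to 806.

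**Step 2. Power of the test that will be run.** Expected evaluable patients: 403 × 0.95 = 382.85, so 383 per arm. Power was obtained by enumerating both binomial distributions in full and summing the probability of every table in which the test gives two-sided p < 0.05.

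| Evaluable per arm | Fisher | Pearson chi-square, uncorrected |
|---|---|---|
| 382 | 76.6% | 80.9% |
| 383 (5% dropout) | 76.7% | 81.0% |
| 403 (no dropout) | 79.1% | 83.0% |

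**Step 3. Size needed for Fisher.** Power is 79.99% at 411 per arm and 80.1% at 412. 412 / 0.95 = 433.7, rounded up to 434 per arm and 868 in total, which is 868 − 806 = 62 more than planned.

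**Step 4. Why power is lost.** True type I error with 383 per arm when both arms share the same rate:

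| Common rate | Fisher | Chi-square |
|---|---|---|
| 2.8% | 3.2% | 4.9% |
| 5.0% | 3.4% | 4.8% |
| 7.2% | 3.7% | 4.9% |

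At 5%, Fisher leaves (5.0 − 3.4) / 5.0, about a third, of the permitted error unused.

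**Step 5. What this means in cases.** The plan implies about 383 × 0.028 = 10.7 detections in the US arm and 383 × 0.072 = 27.6 in the HBP-AMRI arm. With 11 in the US arm, chi-square is significant from 23 HBP-AMRI detections and Fisher from 24. For every US count from 8 to 14, Fisher requires exactly one more detected cancer.

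**Step 6. Is chi-square safe here?** At a common rate of 5%, 383 × 0.05 = 19 events are expected per arm, well above the usual threshold of 5.

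**The case against.** The arithmetic is not in dispute. The case on the other side concerns weight and remedy.

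- **Fisher is valid.** Its error is on the conservative side, so a positive result stands and nothing is biased. This is right: the cost is type II error only, about 23% instead of 20%.
- **The sizing test is inferred.** The article names neither z nor chi-square. That is true, and the unpooled formula that gives 403 is not identical to the pooled Pearson test (405). The shortfall does not depend on the inference, however: whatever formula was used, Fisher at 806 with 5% dropout does not give 80%.
- **Dropouts may stay in the denominator.** The Outcomes section divides by all patients under surveillance and does not say that dropouts are removed. If all 403 per arm count, Fisher has 79.1%. This narrows the gap to 0.9 points but does not close it.
- **Other uncertainty is larger.** Fisher power at 383 per arm is 70.1% if prevalence is 7%, 82.2% if it is 9%, and 65.8% if US sensitivity is 40%. This is true and keeps the point in proportion, but uncertain rates do not make the power stated at the assumed rates correct.
- **Changing the test mid-trial has a price.** The trial is open-label and has recruited since August 2022, so moving to a more powerful test can look data-driven, and the article requires ethics board approval for any protocol change. This stands, and it governs how the change must be made.
- **Chi-square is not guaranteed exact.** With 403 per arm its size reaches 5.02% at a common rate near 7.7%. The excess is trivial.

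**Conclusion.** The concern holds. Under the plan's own rates and 5% dropout, the stated primary test has 76.7% power, 3.3 points below the stated 80%; with full retention it has 79.1%. The figures rest on 7.2% v 2.8%, equal arms, a two-sided Fisher p-value below 0.05, and dropouts leaving the denominator in the first case and staying in it in the second. That the sample size came from an uncorrected normal formula is an inference, supported by an exact match. The loss is modest and does not threaten the validity of a positive finding, but the power claim and the named analysis do not belong together and should be reconciled.

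**What to change.** Choose one of two routes and make the Sample size and Statistical analysis sections agree.

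1. **Change the test (preferred).** Name the uncorrected Pearson chi-square test as primary for early-stage detection, and report the risk difference with a 95% confidence interval. This gives 81.0% power at 383 per arm, with true size at or very near 5%. If a guaranteed bound on type I error is wanted, name Boschloo's unconditional exact test, which is never less powerful than Fisher's; its power was not computed here.
2. **Keep Fisher.** State that power is about 77% after 5% dropout (79% with none).

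Neither route needs more patients; holding 80% with Fisher by enrolment would take 62 more.

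The first route costs one sentence and a protocol amendment with ethics board approval. Because the trial is open-label, the amendment should be dated and made before anyone examines outcomes by arm, and it should give the reason, namely agreement with the sample size calculation. Waiting until just before data lock would be weak protection. The second route costs only a corrected statement of power.

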### Eligibility criteria

#### Inclusion criteria

Adults aged ≥20 years.Diagnosis of liver cirrhosis based on at least 1 of the following:Histological confirmation via liver biopsy, orRadiologic evidence of cirrhosis and portal hypertension, defined as typical imaging features of liver cirrhosis on radiologic examination with liver stiffness ≥12 kPa on transient elastography or the presence of esophageal or gastric varices.High risk for HCC (estimated annual risk >5%), defined as a risk index ≥2.33:Risk index=1.41 (if age ≥50 y) + 1.65 (if prothrombin activity ≤75%) + 0.92 (if platelet count ≤100 × 10^3^/μL) + 0.74 (if positive for anti-HCV or HBsAg).^26^
Eastern Cooperative Oncology Group performance status 0–2.No history or current evidence of HCC within 6 months prior to enrollment.Willing and able to provide written informed consent and comply with study procedures.

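### The primary Fisher exact test has about 77% power, not the planned 80%, and leaves unused a risk index known for every participant at screening

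*Protocol article*

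**What the plan says.** The primary endpoint is the proportion of patients under surveillance whose BCLC 0 or A HCC is detected by the assigned modality (Outcomes). The test is named in Statistical analysis: "Detection rates and the rate of curative treatment will be compared using the Fisher exact test".

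The same section allows for modelling, but only conditionally: "If appropriate, multivariable logistic regression analyses will be used to determine the independent associations between variables". It names no covariates and does not tie the model to the primary comparison.

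Under Inclusion criteria, entry requires "High risk for HCC (estimated annual risk >5%), defined as a risk index ≥2.33". The index is a weighted sum of four binary items (age, prothrombin activity, platelet count, viral status) with weights 1.41, 1.65, 0.92 and 0.74. Enrollment and allocation describes permuted blocks and mentions no stratification factor.

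Under Sample size, "we assumed detection rates of 7.2% for HBP-AMRI and 2.8% for US", "with 80% power and a 2-sided alpha of 0.05", with 5% dropout, giving 403 per arm.

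**The concern.** The detection rate depends on two things: who develops early-stage HCC, and whether the modality finds it. The trial measures a predictor of the first for everyone before randomisation, uses it as an entry gate, and then leaves it out of the primary comparison. The article's own Discussion presents quantitative risk selection as a distinguishing feature of the trial.

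The chosen test is also conservative when events are few, while the sample size appears to come from a normal-approximation formula. The stated 80% power therefore may not belong to the test that will be run. At stake is a few points of power in a trial that expects about 38 primary events: 383 × (0.072 + 0.028) = 38.3.

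**Working it through.** **1. Reproducing the planned size.** Inputs from Sample size: 8% cumulative prevalence, sensitivities 90% and 35%, so 0.08 × 0.90 = 7.2% and 0.08 × 0.35 = 2.8%; two-sided alpha 0.05; power 80%; dropout 5%.

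Unpooled normal approximation, per arm:

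n = (1.960 + 0.842)² × [0.072 × 0.928 + 0.028 × 0.972] / (0.072 − 0.028)² = 7.849 × 0.09403 / 0.001936 ≈ 381.2, rounded up to 382.

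382 / 0.95 = 402.1, rounded up to 403 per arm, 806 in total. This matches the article. The pooled formula gives 384 (405 per arm) and the continuity-corrected formula 429 (452 per arm), so the stated size makes no allowance for Fisher's conservatism.

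**2. Power of the test actually named.** Exact enumeration of the two-sided Fisher test at 7.2% v 2.8%:

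- 382 per arm: 76.6%
- 383 per arm: 76.7%
- 403 per arm (no dropout): 79.1%

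Its actual size at a common rate of 5% is about 3.4%. Fisher reaches 80% at about 413 evaluable per arm, or 435 after dropout.

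**3. Range of the index.** Maximum 1.41 + 1.65 + 0.92 + 0.74 = 4.72. The lowest qualifying score is 1.41 + 0.92 = 2.33. Enrolled patients therefore lie between 2.33 and 4.72.

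**4. What adjustment adds.** Simulation with 383 per arm and 3,000 trials per scenario. The index was built from the printed weights and truncated at 2.33. Prevalence followed a logistic function of the index averaging 8%, multiplied by sensitivity 0.90 or 0.35. Two things are assumed because the article gives neither:

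- Frequencies of the four items, in the order listed above: mix A 85/35/45/75% (index SD 0.74); mix B 80/50/50/60% (SD 0.78).
- The log-odds slope per index unit, close to a log-risk slope at this prevalence.

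Power in %, mix A / mix B:

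| Slope | Fisher | Chi-square | Adjusted score | Unadjusted LRT | Adjusted LRT |
|---|---|---|---|---|---|
| 0 | 76.9 / 76.0 | 81.9 / 80.0 | 82.1 / 80.5 | 83.0 / 81.2 | 82.7 / 81.2 |
| 0.5 | 76.3 / 77.6 | 80.9 / 81.9 | 81.3 / 82.5 | 82.0 / 83.2 | 81.7 / 83.1 |
| 1.0 | 75.9 / 77.3 | 80.7 / 81.7 | 81.9 / 82.8 | 82.1 / 82.5 | 82.2 / 83.2 |
| 1.5 | 77.0 / 76.6 | 81.8 / 80.7 | 84.2 / 83.1 | 83.0 / 82.0 | 84.5 / 83.3 |

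Simulation error is about 0.8 points on each figure; paired differences are tighter.

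**5. Splitting the gain.** Moving from Fisher to the unadjusted chi-square adds about 4 to 5 points. The like-for-like contribution of the index is:

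- Score test against chi-square: 0.2 to 0.6 points at slopes 0 to 0.5, 1.2 at slope 1.0, 2.4 at slope 1.5.
- Adjusted against unadjusted LRT: −0.3 to 0 at slopes 0 to 0.5, 0.1 to 0.7 at slope 1.0, 1.3 to 1.5 at slope 1.5.

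Separate runs of 6,000 trials with other item frequencies gave score-test gains of 1.7 points (80.9 to 82.6%) and 2.0 points (80.7 to 82.7%) at slope 1.0, and 0.6 points (80.7 to 81.3%) at slope 0.5. For slopes 0 to 1 the covariate is thus worth roughly 0 to 2 points.

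**6. Type I error.** With 5% in both arms and slope 1.0 (4,000 trials), rejection was 3.6% for Fisher, 5.2% for chi-square, 5.4% for the adjusted score test and 5.5% for the adjusted LRT. Across all runs the adjusted tests lay at about 5.1 to 5.8%.

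**The case against.** An unadjusted test of two proportions in a 1:1 randomised trial is valid, and it matches both the endpoint and the contrast that was powered. Further adjusted analyses may sit in an analysis plan that is not shown. Fisher guarantees a type I error of at most 5%; the alternatives are asymptotic, with about 38 events. Logistic regression targets a conditional odds ratio, so a further step is needed to return to the difference in detection rates. The article does not say how prognostic the index is among enrolled patients, and the index predicts developing HCC rather than having it detected at BCLC 0 or A.

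Most of this stands, and it limits the point to efficiency. It does not remove it: the article names the primary test, that test cannot take a covariate, and its power is below the figure on which the trial was sized.

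A reader might infer more, in four ways that the document does not support:

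- **That the index yields the whole step from 77% to 81–83%.** It does not; an unadjusted chi-square already recovers most of it.
- **That adjustment is free.** It gives up exact size control and adds standardisation.
- **That an imbalance in risk would bias the comparison.** Chance imbalance is already covered by the test's error rate, and the article describes concealed allocation, with the code opened only after consent.
- **That risk varies about 11-fold across enrolled patients.** exp(4.72 − 2.33) = exp(2.39) ≈ 10.9 contrasts only the two extreme scores and assumes that the index is a log-risk, which the article does not say.

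**Conclusion.** The point holds as a modest loss of efficiency. The planned Fisher test has 76.6 to 76.7% power at 382 to 383 evaluable per arm, about 3 points short of the stated 80%. This shortfall follows from the article's own inputs alone. An index-adjusted logistic score or likelihood-ratio test has about 81 to 83%.

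The part due to the index, roughly 0 to 2 points, is less certain. It rests on assumed item frequencies and an assumed log-risk slope of 0 to 1 per unit within 2.33 to 4.72. If the index is not prognostic in that range, its contribution is essentially nil; in the simulations at slope 0, including it changed power by no more than about 0.4 points either way. The result would matter only for borderline outcomes.

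**What to change.** Before any comparative analysis, name as the primary analysis a logistic regression of early-stage HCC detection (yes/no) on arm and the continuous screening risk index, with the arm effect tested two-sided at 5%. Choose the score or the likelihood-ratio test in advance. Report the standardised risk difference with its 95% CI, obtained by averaging predicted probabilities under each arm over the analysed patients, so that the reported effect stays on the scale that was powered. Keep the Fisher exact test as a sensitivity analysis.

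This takes a sentence or two of analysis wording and needs no new data, since the index is collected for eligibility. One covariate on about 38 events is feasible. Because the trial is open-label and follow-up is ongoing, the change should be fixed and dated before outcomes are compared by arm. The sponsor accepts a simulated size of about 5.1 to 5.8% in place of an exact guarantee. Which patients form the analysis population is a separate matter and is left as it is here.

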### Participant flow

A trained research coordinator introduced the trial to potentially eligible patients during outpatient clinic visits or scheduled assessments. Patients who met all eligibility criteria received comprehensive verbal and written information about the study’s objectives, procedures, risks, and potential benefits. Adequate time was provided for consideration, and informed discussions with investigators were encouraged. Written informed consent was obtained from those who agreed to participate.

Upon enrollment, participants were randomly assigned in a 1:1 ratio to undergo 2 consecutive rounds of HCC surveillance using either biannual US or biannual HBP-AMRI at 6-month intervals (with a variation of ±1 mo allowed) (Figure 1). The first surveillance test is scheduled for ~6 months after the participant’s last imaging study, confirming the absence of hepatic malignancy.

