**FIGURE 1 F1:**
[figure not shown]
Participant flow. Abbreviations: HBP-AMRI, hepatobiliary phase-abbreviated magnetic resonance imaging; LR, Liver Imaging Reporting and Data System category; US, ultrasonography.

If a lesion is detected and considered potentially malignant based on predefined radiologic criteria (see *Imaging Evaluation* section below), a confirmatory imaging test will be conducted. Participants with no suspicious findings will proceed to the second surveillance round at the scheduled interval. Following completion of the second surveillance round, all participants will enter a 6-month observation period, during which delayed HCC diagnosis and clinical outcomes will be assessed. If a “positive” lesion is ultimately determined to be a false-positive following the confirmatory test, the participant will return to their assigned surveillance schedule.

Dropout will be defined as: (1) withdrawal of consent or determination by the investigators that the participant is unable to adhere to the protocol; (2) liver transplantation without prior HCC diagnosis, (3) diagnosis of extrahepatic malignancy during the study period, or (4) failure to complete one or more consecutive scheduled surveillance visits. To minimize dropouts, participants will receive up to 2 reminders per visit (3 d and 1 d in advance) via phone call or text message. In addition, staff will offer flexible scheduling support and follow-up if participants miss or need to reschedule an appointment.

Peripheral blood samples will be collected at the screening visit and at each surveillance visit for all enrolled participants following approved protocols. Serum levels of alpha-fetoprotein and protein induced by vitamin K absence-II will be measured at each visit. Stored samples may be used in future ancillary studies. Written informed consent will be obtained from all enrolled participants for specimen collection and future use.

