### Imaging evaluation

All surveillance imaging studies will be interpreted by board-certified abdominal radiologists using a standardized 3-point scale reflecting the likelihood of HCC: positive, subthreshold, and negative (Table 1). Participants with a “positive” result on either modality will undergo confirmatory testing, while those with a “subthreshold” or “negative” result will proceed to the next scheduled surveillance in 6 months.

**TABLE 1 T1:** Lesion categorization on HBP-AMRI and US

Category	HBP-AMRI	US
	Definition	Definition
Positive	▪ A new solid nodule ≥10 mm is not definitely benign^a^ ▪ Changes in imaging characteristics^b^ or threshold growth^c^ of a previous subthreshold observation ▪ New thrombus in the vein	• A new solid nodule or parenchymal distortion ≥10 mm distinct from the background liver • Threshold growth^c^ of previous subthreshold observation • New thrombus in the vein
Subthreshold	▪ Solid nodule <10 mm, not definitely benign^a^ ▪ Previous positive observation confirmed as a false positive	• Solid nodule or parenchymal distortion <10 mm • Previous positive observation confirmed as a false positive
Negative	▪ No observation ▪ Only definitely benign observation^d^	• No observation • Only definitely benign observation^d^

^a^
Mild to moderate hyperintensity on T2-weighted imaging, diffusion restriction, or hypointensity on hepatobiliary-phase imaging.

^b^
Any new appearance of not definitely benign characteristics.

^c^
Size increase by ≥50% in ≤6 months.

^d^
Cyst, hemangioma, or other previously characterized benign lesion.

Abbreviations: HBP-AMRI, hepatobiliary phase-abbreviated magnetic resonance imaging; US, ultrasonography.

For HBP-AMRI, a “positive” result is defined as the presence of a new solid nodule ≥10 mm that does not demonstrate definitely benign characteristics (mild to moderate hyperintensity on T2-weighted imaging, diffusion restriction on diffusion-weighted imaging, or hypointensity on HBP imaging), changes in imaging characteristics or threshold growth of a previous subthreshold observation, or development of new thrombus in vein (TIV). Benign entities such as cysts, hemangiomas, and previously characterized benign lesions are not considered positive, regardless of size.

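### False referral is counted per examination, with up to two per participant, but the named tests make no stated allowance for within-participant correlation

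*Protocol article*

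**What the plan says.** All references are to the protocol article.

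- **Unit.** Outcomes: "False referral rate is defined on a per-exam basis", and the count of false referrals is "divided by the total number of surveillance tests performed in that modality arm".
- **Examinations per participant.** Participant flow: participants are randomised "to undergo 2 consecutive rounds of HCC surveillance using either biannual US or biannual HBP-AMRI at 6-month intervals". After a false positive, "the participant will return to their assigned surveillance schedule" (same section, text after Figure 1). One person can therefore supply two entries to the denominator and, in principle, two to the numerator.
- **Repeat referral.** In Table 1 (Imaging evaluation), the subthreshold category includes "Previous positive observation confirmed as a false positive" for both modalities. The table also makes a subthreshold observation positive on threshold growth or, for HBP-AMRI only, on changed imaging characteristics.
- **Tests.** Statistical analysis: "False referral rates will be compared using Fisher exact test or Poisson regression analysis". Associations of image quality with Child–Pugh class, detection and false referral "will be examined using chi-square or Fisher exact tests as appropriate". The level is two-sided 0.05. The section mentions neither clustering nor a robust variance, and no confidence interval for false referral.
- **Status.** The Discussion treats false referral as a key secondary endpoint that captures unnecessary procedures, anxiety and resource use.

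**The concern.** Randomisation is by participant, but this endpoint is counted by examination. Two examinations of the same liver six months apart need not be independent. A nodular or heterogeneous liver may produce false positives in both rounds, which would make the correlation positive. The rule that a refuted lesion becomes subthreshold works the other way, because the same lesion is not normally referred twice.

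Fisher's exact test on a table of examinations has no place for this correlation. Poisson regression can accommodate it, but only with a variance that the text does not mention. The two methods are joined by an *or*, with no rule for choosing between them in an open-label trial.

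At stake is the harm side of the comparison. A gain in early detection will be weighed against the difference in false referrals, so the precision attached to that difference should be right.

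**Working it through.** **The plan's own figure.** The article gives no rate, power or sample size for false referral. The only figure to reproduce is the primary-endpoint sample size, which supplies the number per arm. With 7.2% versus 2.8%, two-sided 0.05 and 80% power:

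n = (1.960 + 0.842)² × (0.072 × 0.928 + 0.028 × 0.972) / 0.044² = 381.2, so 382. Then 382 / 0.95 = 402.1, so 403 per arm and 806 in total. This matches the plan.

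**Inputs for the check**
- Participants per arm: 403 × 0.95 = 382.85, taken as 383.
- Examinations per arm: at most 2 × 383 = 766. Two per participant is a maximum, since HCC found in round 1 or dropout leaves one.
- False referral rate p: assumed 7%, with 3% to 15% as the range. The Introduction cites HBP-AMRI specificity of 91.0% to 93.2%, which implies about 7% to 9% false positives, but from retrospective diagnostic studies.
- Within-participant correlation ρ: not in the documents; a range is shown. Its lower limit, reached when nobody has two false referrals, is −p/(1−p) = −0.07/0.93 = −0.075.

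**Effect on the standard error.** With two examinations each, the variance of an arm's rate is p(1−p)/(2n) × (1+ρ). The true SE is therefore √(1+ρ) times the independence SE: 1.05 at ρ = 0.1, 1.10 at 0.2, 1.14 at 0.3 and 1.22 at 0.5.

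At 7% in both arms, the independence SE of the difference is √(2 × 0.07 × 0.93 / 766) = 0.0130, a 95% half-width of 2.6 percentage points. The correct half-width would be 2.5 points at ρ = −0.075, 2.9 at 0.3 and 3.1 at 0.5.

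**The Poisson option.** With arm as the only covariate, the model-based SE of the log rate ratio is √(1/e₁ + 1/e₀), where e is the number of false referrals in each arm. This is the same whether the model is fitted to examinations or to participant counts with the number of examinations as offset. The true SE is √((1−p)(1+ρ)) times that. At p = 7% the two agree only at ρ = 0.07/0.93 = 0.075. Below that value the Poisson SE is too large (by 1/√0.93 = 1.037 at ρ = 0), and above it too small.

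**Simulated type I error.** Correlated binary pairs, 383 participants per arm, no true difference, 20,000 replicates, p = 7%:

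| ρ | Fisher, per examination | Poisson, model-based SE | Clustered on participant |
|---|---|---|---|
| −0.075 (no repeats) | 0.031 | 0.032 | 0.049 |
| 0 | 0.040 | 0.042 | 0.049 |
| 0.1 | 0.048 | 0.050 | 0.048 |
| 0.2 | 0.064 | 0.066 | 0.052 |
| 0.3 | 0.069 | 0.071 | 0.046 |
| 0.5 | 0.094 | 0.097 | 0.048 |

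Across rates of 3% to 15%, Fisher runs from 0.025 to 0.034 with no repeats, 0.041 to 0.053 at ρ = 0.1, 0.064 to 0.076 at 0.3 and 0.086 to 0.097 at 0.5. The clustered analysis stays between 0.045 and 0.054 throughout.

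**What these correlations mean.** The chance of a second false referral after a first is p + ρ(1−p). At p = 7% that is 16% at ρ = 0.1, 26% at 0.2, 35% at 0.3 and 54% at 0.5.

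**The case against.** The strongest reply is that no error has been shown, only the possibility of one. The correlation is unknown. With the subthreshold rule in Table 1, a repeat referral needs a different new finding, threshold growth or, on HBP-AMRI, changed characteristics. A correlation near or below zero is therefore at least as plausible as 0.3, which would mean a 35% chance of a second false referral against a base rate of 7%. In that case the named tests are conservative, and Fisher's own conservatism absorbs part of any inflation. This stands, and it limits the finding to a modest error of unknown direction. A reader might infer that the false referral p-values are simply wrong, or too small. The documents do not support that. Nor can planned confidence intervals be called wrong, since none is mentioned for this endpoint.

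A second reply is that Poisson regression may be intended with a clustered variance, a detail a condensed article can leave to the full protocol or analysis plan. This stands in part: the Poisson option cannot be called an independence analysis with certainty. But refitting on participant counts is not enough, because the model-based arm comparison does not change. Fisher on examinations is a named alternative with no such escape.

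A third reply is that the per-examination unit is deliberate and suits an endpoint about unnecessary work-ups. That stands in full. A reader might conclude that the unit is itself an error and must become per participant, but that would be a preference.

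Finally, the unit of the image-quality tests is not stated, so that part of the point is conditional.

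**Conclusion.** The point holds as a mismatch between a stated unit and a stated test. False referral is measured on examinations nested in randomised participants, and the comparison as written is valid only if within-participant correlation is negligible. On assumed values (7% rate, two examinations each, 383 participants per arm), the nominal 5% Fisher test runs at about 3% with no repeats, about 5% at ρ = 0.1, 6 to 7% at 0.2 to 0.3, and 9% at 0.5. The rate and ρ are assumptions, and the direction of the error cannot be known in advance.

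The primary endpoint, a per-patient detection rate, is not touched, and neither is the sample size. This should be corrected before analysis because false referral is a key secondary endpoint, but it does not threaten the trial's main conclusion.

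**What to change.** In Statistical analysis, replace the choice between Fisher and Poisson with one prespecified method that accounts for the participant. For example:

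> *False referral will be compared between arms at examination level by GEE (or modified Poisson regression) with robust variance clustered on participant, and reported as a rate difference or rate ratio with 95% confidence interval.*

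The final text should settle on one model and one effect measure. If the full protocol or analysis plan already specifies this, the article's sentence only needs to be aligned with it.

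State the unit for the image-quality association tests and, if it is the examination, use the same clustering. The number and percentage of participants with at least one false referral may be added as a supportive description, not as a replacement endpoint.

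The cost is analysis wording only. Data are entered at each surveillance visit under a unique participant number (Data collection and management), so nothing further need be collected. Follow-up is ongoing, so the choice can still be fixed before analysis.
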